### III. Statistical Analysis Plan

#### Food Prescription Trial: Statistical Analysis Plan 9 March 2025

##### 1. Background

Over 4 million Canadians (or 12.4 % of households) experience food insecurity defined as the inadequate or insecure access to food due to financial constraints (1). Most likely to experience food insecurity are people who live on low incomes, including those who receive social assistance in cities with high costs of living (1–3). Food insecurity is associated with increased risk for type 2 diabetes (4), as well as poor glycemic control and diabetes distress for those already diagnosed (5–7). Individuals with a low income and diabetes or prediabetes are less likely to adhere to dietary management guidelines and are at an increased risk of developing complications (8–10). Food insecurity is correlated with reduced diet quality and lower consumption of healthy foods in adults with diabetes (11). Facilitating access to healthy foods could free up money for the purchase of other needed goods or services.

##### 2. Trial

The Food Prescription study was a randomized-controlled trial that measured the effects of a monthly food voucher on diabetes-related health outcomes. Participants were randomized to either to the control group, where they would continue to receive usual clinical care, or to the intervention group, where they received a monthly subsidy of \$65 or \$85 for healthy food every month for six months on top of their usual clinical care. Outcomes were measured at 6 months. Whether participants received a \$65 or \$85 monthly voucher was determined by the number of individuals in the household, most participants received \$65 monthly and those living in households with more than 5 members received \$85 monthly.

###### 2.1 Primary Research Question

In adults with type 2 diabetes or “prediabetes” experiencing either food insecurity or trouble making ends meet, what is the effect of a \$65 (or \$85) monthly food voucher for six months on the change in hemoglobin A1c values?

###### 2.2 Trial Design

We conducted an open label, parallel two-arm, 1:1 allocation randomized controlled trial. Randomization is stratified by condition: “pre-diabetes” (A1c 6.0 to 6.4) versus diabetes (A1c  $\geq$  6.5).

##### 3. Objectives

###### 3.1 The primary objective of this trial is to test the following hypothesis:

1. A monthly subsidy of \$65 (or \$85) for healthy food every month for six months is superior to usual care in decreasing HbA1c levels after 6 months in adults with type 2 diabetes or “prediabetes” experiencing food insecurity or trouble making ends meet

###### 3.2 The secondary objectives of this trial are to test the following hypotheses:

1. A monthly subsidy of \$65 (or \$85) for healthy food every month for six months is superior to usual care in its effect on beta-carotene in adults with type 2 diabetes or “prediabetes” experiencing food insecurity or trouble making ends meet

2. A monthly subsidy of \$65 (or \$85) for healthy food every month for six months is superior to usual care in its effect on ascorbic acid in adults with type 2 diabetes or “prediabetes” experiencing food insecurity or trouble making ends meet
3. A monthly subsidy of \$65 (or \$85) for healthy food every month for six months is superior to usual care in its effect on self-reported health status in adults with type 2 diabetes or “prediabetes” experiencing food insecurity or trouble making ends meet
4. A monthly subsidy of \$65 (or \$85) for healthy food every month for six months is superior to usual care in its effect on self-reported financial security in adults with type 2 diabetes or “prediabetes” experiencing food insecurity or trouble making ends meet
5. A monthly subsidy of \$65 (or \$85) for healthy food every month for six months is superior to usual care in its effect on food security status in adults with type 2 diabetes or “prediabetes” experiencing food insecurity or trouble making ends meet
6. A monthly subsidy of \$65 (or \$85) for healthy food every month for six months is superior to usual care in its effect on self-reported vegetable consumption in adults with type 2 diabetes or “prediabetes” experiencing food insecurity or trouble making ends meet
7. A monthly subsidy of \$65 (or \$85) for healthy food every month for six months is superior to usual care in its effect on self-reported fruit consumption in adults with type 2 diabetes or “prediabetes” experiencing food insecurity or trouble making ends meet

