  - a. (If answered Yes to question 3) How often did this happen? Potential responses are: Almost every month, Some months but not every month, Only 1 or 2 months, Don't know/Refuse to answer
4. In the past 6 months, did you (personally) ever eat less than you felt you should because there wasn't enough money to buy food

5. In the past 6 months, were you (personally) ever hungry but didn't eat because you couldn't afford enough food? Potential responses are: Yes, No, Don't know/Refuse to

Participants can answer affirmatively to 0 to 6 of the questions. We will assess food security status as a binary variable, where less than 2 affirmative responses indicates "food secure" and 2 or more affirmative responses indicates more "food insecure." This is based on Health Canada's approach to interpreting the data from the Household Food Security Survey Module (13). We will also examine food security as a raw score between 0 to 6 (based on the number of affirmatively answered questions) as a sensitivity analysis.

Self-reported financial security is a categorical variable where participants were asked the standard question at follow-up "Do you have trouble making ends meet at the end of the month?" Potential responses were: yes, no and decline to respond.

Self-reported vegetable consumption and self-reported fruit consumption are both categorical variables, measured at both baseline and 6 months. Participants were asked "How often to you eat vegetables?" and "How often do you eat fruits?" Potential responses included: 0 times per day, once per day, twice per day, three times per day, four times per day, five or more times per day, or decline to answer.

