### 6.3 Secondary Outcomes:

1. Serum  $\beta$ -carotene levels (a continuous variable, expressed in units of  $\mu\text{mol/L}$ )
2. Serum ascorbic acid levels (a continuous variable, expressed in units of  $\mu\text{mol/L}$ )
3. Self-reported health status (an ordinal variable with the following categories: very good, good, moderate, bad, and very bad)
4. Self-reported financial security (a binary variable with the following categories: yes and no)
5. Self-reported food security (an ordinal variable with values between 0 to 6 and a binary variable with the following categories: food secure and food insecure)

6. Self-reported vegetable consumption (a count variable with values between 0 to 5 times per day)
7. Self-reported fruit consumption (a count variable with values between 0 to 5 times per day)

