### 8.3 Analysis of secondary outcomes

The continuous outcomes of serum  $\beta$ -carotene and ascorbic acid levels will be compared between groups using difference in means with 95% confidence intervals, and t-tests will be used to derive two-sided  $p$ -values. Alternative non-parametric tests will be used if the data does not meet the assumptions of t-tests and these may include the Wilcoxon Rank Sum test.

The binary outcomes of self-reported financial security and food security status will be compared between groups using risk differences with 95% confidence intervals, and chi-squared tests to derive two-sided  $p$ -values.

The count outcomes of self-reported vegetable and fruit consumption, will be compared between groups using the Wilcoxon rank sum test, where a  $p$ -value of  $<0.05$  will be sufficient to reject the null hypothesis of no difference.

For the ordinal outcomes of self-reported health-status and food-security score ordinal regression will be used using odds ratios with 95% confidence intervals.

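### The SAP sets seven secondary superiority hypotheses with no multiplicity control, testing order or exploratory label; if each is judged at two-sided 0.05, the chance of at least one false significant result is up to about 30% (about 16% favouring the voucher).

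*Combined protocol and SAP*

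**What the plan says.** SAP 3.2 introduces the secondary objectives with "The secondary objectives of this trial are to test the following hypotheses". Seven follow: beta-carotene, ascorbic acid, self-reported health, financial security, food security status, vegetable consumption and fruit consumption. Each has the same directional form; the last, for example, says that the subsidy "is superior to usual care in its effect on self-reported fruit consumption in adults with type 2 diabetes" (prediabetes is named as well). The primary hypothesis in SAP 3.1 is also worded as superiority over usual care.

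SAP 8.3 treats the seven in different ways:

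- **Beta-carotene and ascorbic acid.** The text reads "will be compared between groups using difference in means with 95% confidence intervals, and t-tests will be used to derive two-sided" (the object is the p-value). No threshold is given.
- **Financial security and food security status.** The text reads "will be compared between groups using risk differences with 95% confidence intervals, and chi-squared tests to derive two-sided" (again, the object is the p-value). No threshold is given.
- **Health status** gets an odds ratio with a 95% confidence interval from ordinal regression. Neither a p-value nor a threshold is mentioned.
- **Vegetables and fruit** get a Wilcoxon test, with this rule: "where a $p$ -value of $<0.05$ will be sufficient to reject the null hypothesis of no difference".

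The 0.05 rule in SAP 8.2 is limited to the primary analysis.

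Food security appears in two forms. SAP 6.3 lists the secondary outcome both as an ordinal score from 0 to 6 and in binary form, and 8.3 gives the score its own ordinal regression. SAP 5.3 gives the score the lower rank of a sensitivity analysis: "We will also examine food security as a raw score between 0 to 6 (based on the number of affirmatively answered questions) as a sensitivity".

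The protocol's outcome and analysis text adds no adjustment, testing order or exploratory label.

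**The concern.** Objectives framed as superiority hypotheses to be tested, with a stated rejection rule for two of them, read as grounds for claims. Nothing in the plan says how a positive secondary is to be read when several were tested, or when HbA1c shows no difference. As written, one p-value below 0.05 among seven could be reported as superiority on that outcome even if the primary is null.

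The setting makes such a result easy to promote. The trial is open label, and five of the seven outcomes are self-reported (health, financial security, food security, vegetables, fruit). Lack of blinding is a separate source of bias and does not enter the chance figures below, but it is a further reason not to let an isolated self-reported result stand as a finding of superiority.

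The food-security score adds a smaller problem. Its standing differs between SAP 5.3 and SAP 6.3 and 8.3, so a positive score beside a null binary result could be presented either as a secondary finding or as a sensitivity analysis.

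**Working it through.** **The plan's own figure.** The documents give no error rate for the secondary outcomes as a set, so there is none to reproduce. The one related figure is the primary sample size in SAP 7 (difference 0.4, SD 1.3, alpha 0.05, power 80%). Read as two-sided:

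n per arm = 2 × (1.960 + 0.842)² × (1.3/0.4)² = 165.8, rounded up to 166, or 332 in total.

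This matches the SAP and shows that its alpha is two-sided 0.05.

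**Inputs**

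- Number of hypotheses: 7 (SAP 3.2).
- Level per test: two-sided 0.05. This is explicit for vegetables and fruit. For the other five it is an assumption, based on the two-sided p-values and 95% intervals in SAP 8.3.
- Correlation between test statistics: not in the documents, so a range is shown.
- Scenario: no true effect on any of the seven.

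**Independent tests**

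- At least one significant result in either direction: 1 − 0.95⁷ = 0.302.
- At least one significant result favouring the voucher (0.025 per test): 1 − 0.975⁷ = 0.162.
- The two outcomes with an explicit rule alone: 1 − 0.95² = 0.0975 in either direction.

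**Correlated tests.** Simulation of seven equally correlated standard normal statistics, 1,000,000 draws for each correlation:

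| Assumed correlation | Either direction | Favouring the voucher |
|---|---|---|
| 0 | 30.2% | 16.2% |
| 0.3 | 27.2% | 13.7% |
| 0.5 | 23.0% | 11.4% |
| 0.7 | 17.8% | 8.9% |
| 0.8 | 14.8% | 7.4% |
| Single test, for comparison | 5% | 2.5% |

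Equal correlation across all seven is a simplification. Suppose instead that only related outcomes correlate: the two serum markers with vegetables and fruit, and financial with food security. A within-group correlation of 0.5 then gives 27.1% in either direction and 14.3% favouring the voucher; 0.7 gives 24.4% and 12.6%.

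**The food-security score as an eighth test.** The score and the binary status come from the same answers, so their tests cannot be treated as independent. With a correlation of 0.7 to 0.9 between those two and the other six independent, the either-direction figure is 32.6% to 31.7%, against 30.2% for seven tests. The score adds little to the error rate; the difficulty is its unclear standing.

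**The case against.** The strongest reply is that these outcomes are labelled secondary, there is one primary outcome with its own 0.05 test, and the documents nowhere promise 5% across the secondary set. All of that is true, and the primary error rate is untouched. But the label does not settle how a positive result may be used when the SAP also says that these are superiority hypotheses to be tested.

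Three stronger readings are tempting and do not hold:

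- **That every secondary is tested at 0.05.** A reader might infer this from SAP 3.2. SAP 8.3 states the rule for two outcomes only, and the seven-test figures depend on extending it to the rest.
- **That a false superiority result has a 23 to 30% chance.** That range counts results in either direction, including the voucher doing worse. In favour of the voucher it is about 11 to 16% over the same correlations (0.5 to 0), and lower if correlation is stronger.
- **That hypothesis 5 has two tests of equal rank.** SAP 3.2 refers to food security status, 5.3 defines status as the binary variable, and 8.3 keeps status and score apart. What remains is the conflict between 5.3, which calls the score a sensitivity analysis, and 6.3 and 8.3, which list it as an outcome.

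It may also be said that one sentence calling for cautious interpretation would be enough. It would help, but it would leave the superiority wording in 3.2 and the rejection rule in 8.3 in place. Making formal secondary tests conditional on a significant HbA1c result is a debatable trade-off and is not needed to close the gap.

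**Conclusion.** The point holds, and it should be corrected. The SAP sets seven secondary superiority hypotheses and does not say how the error rate across them is handled or that they are exploratory.

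If each is judged at two-sided 0.05 with no true effects, at least one false significant result is expected in about 30% of such trials in either direction, and in about 16% in favour of the voucher, under independence. Positive correlation lowers both, to about 15% and 7% at 0.8. Over the correlations shown this is roughly 3 to 6 times the rate of a single test: 14.8/5 = 3.0 to 30.2/5 = 6.0 in either direction, and 7.4/2.5 = 3.0 to 16.2/2.5 = 6.5 favouring the voucher.

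These sizes rest on two assumptions: that 0.05 is applied to the five outcomes with no stated threshold, and the correlation range. The absence of any multiplicity statement rests on neither. The conclusion on HbA1c is not affected.

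**What to change.** 1. **SAP 3.2.** Replace the wording about testing superiority hypotheses with objectives to estimate the effect of the subsidy on each outcome.
2. **SAP 8.3.** State that secondary outcomes are exploratory, that their p-values are not adjusted for multiplicity, and that no superiority claim will rest on them.
3. **SAP 8.3, vegetables and fruit.** Delete the p<0.05 rejection rule and report an effect estimate with a 95% confidence interval, since the Wilcoxon test as written gives neither. The rate ratio from a quasi-Poisson model, which the protocol already plans for count outcomes with adjustment for baseline, would serve; SAP 5.3 confirms that baseline values were collected.
4. **SAP 6.3 and 8.3.** Name binary food-security status as the test of hypothesis 5, and describe the 0 to 6 score throughout as the sensitivity analysis that 5.3 calls it.

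The cost is SAP wording plus one model for two outcomes. No further data are needed. The downside is that no individual secondary can be claimed as superior on p<0.05 alone.

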#### 4. Study population

##### 4.1 Participant flow

A CONSORT patient flow diagram will be drawn following the CONSORT 2010 standards (<http://www.consort-statement.org/consort-2010>). The flow chart will consider specifically:

- N assessed for eligibility
- N not included in trial (with reasons)
- N randomized
- N allocated to intervention/control
  - N receiving allocated intervention
  - N not receiving allocated intervention (with reasons)
- N followed up at 6 months (with reasons for termination)
- N analyzed
  - N excluded from primary analysis (with reasons)

##### 4.2. Intention-to-treat (ITT) population

The ITT population consists of all randomized participants. Participants will be analysed regardless of whether they actually received the allocated intervention or not or any other protocol deviations in the group they were originally allocated to.

##### 4.3 Complete-cases (CC) population

The CC population consists of all randomized participants who have completed the assessment for the primary outcome data at follow-up.

#### 5. Data Management

### 5.1. Data export

Trial data will be provided by the Applied Health Research Centre and will be imported from the electronic data capturing system into R by the trial statistician for data preparation, validation and analysis.

### 5.2. Data validation

All variables used in the analysis, including the derived variables, will be checked for missing values, outliers, and inconsistencies and queried.

### 5.3 Data preparation

The primary outcome of HbA1c at 6 months will be assessed via laboratory testing for study purposes or review of the electronic primary care record. This is a continuous variable. The primary outcome will be adjusted for HbA1c at baseline, which will be assessed via review of the electronic primary care record. This is a continuous variable.

Serum  $\beta$ -carotene and ascorbic acid levels at 6 months will be assessed via laboratory testing for study purposes.

Data on self-reported food security, self-reported financial security, and self-reported vegetable and fruit consumption will be collected through surveys administered online, over the phone, or in-person at 6 months. Baseline data on self-reported food security and baseline self-reported vegetable and fruit consumption were collected at through surveys conducted over the phone or in-person at the recruitment visit.

Self-reported health status will be measured on a 5-point likert scale, where participants were asked the standard question at follow-up "In general, how would you rate your health today?" Potential responses are: very good, good, moderate, bad, very bad and decline to respond.

Self-reported food security will be assessed using 6 standard and validated items adapted from the Canadian Community Health Survey (Household Food Security Survey Module), applied to the last 6 months (12). The instrument assesses worry about food running out due to financial constraints, food not lasting, and the inability to afford balanced meals using the following questions:

1. The food that you and other household members bought just didn't last, and there wasn't any money to get more. Was that often true, sometimes true, or never true in the past 6 months? Potential responses are: Often true, Sometimes true, Never true, Don't know/Refuse to answer
2. You and other household members couldn't afford to eat balanced meals. Was that often true, sometimes true, or never true in the past 6 months? Potential responses are: Often true, Sometimes true, Never true, Don't know/Refuse to answer
3. In the past 6 months, did you or other adults in your household ever cut the size of your meals or skip meals because there wasn't enough money for food? Potential responses are: Yes, No, Don't know/Refuse to answer
  - a. (If answered Yes to question 3) How often did this happen? Potential responses are: Almost every month, Some months but not every month, Only 1 or 2 months, Don't know/Refuse to answer
4. In the past 6 months, did you (personally) ever eat less than you felt you should because there wasn't enough money to buy food

5. In the past 6 months, were you (personally) ever hungry but didn't eat because you couldn't afford enough food? Potential responses are: Yes, No, Don't know/Refuse to

Participants can answer affirmatively to 0 to 6 of the questions. We will assess food security status as a binary variable, where less than 2 affirmative responses indicates "food secure" and 2 or more affirmative responses indicates more "food insecure." This is based on Health Canada's approach to interpreting the data from the Household Food Security Survey Module (13). We will also examine food security as a raw score between 0 to 6 (based on the number of affirmatively answered questions) as a sensitivity analysis.

Self-reported financial security is a categorical variable where participants were asked the standard question at follow-up "Do you have trouble making ends meet at the end of the month?" Potential responses were: yes, no and decline to respond.

Self-reported vegetable consumption and self-reported fruit consumption are both categorical variables, measured at both baseline and 6 months. Participants were asked "How often to you eat vegetables?" and "How often do you eat fruits?" Potential responses included: 0 times per day, once per day, twice per day, three times per day, four times per day, five or more times per day, or decline to answer.

## 6. Outcomes

### 6.1 Baseline characteristics

The following baseline characteristics will be summarized descriptively by group:

- Age
- Sex
- Gender
- Ethnicity
- Household income
- Income source
- Level of education
- Household size
- Prescribed oral prescription medications
- Prescribed insulin

### 6.2 Primary Outcome

The primary outcome is the change in hemoglobin A1c from baseline to follow up at six months. This is a continuous variable.

### 6.3 Secondary Outcomes:

1. Serum  $\beta$ -carotene levels (a continuous variable, expressed in units of  $\mu\text{mol/L}$ )
2. Serum ascorbic acid levels (a continuous variable, expressed in units of  $\mu\text{mol/L}$ )
3. Self-reported health status (an ordinal variable with the following categories: very good, good, moderate, bad, and very bad)
4. Self-reported financial security (a binary variable with the following categories: yes and no)
5. Self-reported food security (an ordinal variable with values between 0 to 6 and a binary variable with the following categories: food secure and food insecure)

6. Self-reported vegetable consumption (a count variable with values between 0 to 5 times per day)
7. Self-reported fruit consumption (a count variable with values between 0 to 5 times per day)

